# Multi-centre cluster randomised trial comparing a community group exercise programme with home based exercise with usual care for people aged 65 and over in primary care: protocol of the ProAct 65+ trial

**DOI:** 10.1186/1745-6215-11-6

**Published:** 2010-01-18

## Abstract

**Background:**

Regular physical activity reduces the risk of mortality from all causes, with a powerful beneficial effect on risk of falls and hip fractures. However, physical activity levels are low in the older population and previous studies have demonstrated only modest, short-term improvements in activity levels with intervention.

**Design/Methods:**

Pragmatic 3 arm parallel design cluster controlled trial of class-based exercise (FAME), home-based exercise (OEP) and usual care amongst older people (aged 65 years and over) in primary care. The primary outcome is the achievement of recommended physical activity targets 12 months after cessation of intervention. Secondary outcomes include functional assessments, predictors of exercise adherence, the incidence of falls, fear of falling, quality of life and continuation of physical activity after intervention, over a two-year follow up. An economic evaluation including participant and NHS costs will be embedded in the clinical trial.

**Discussion:**

The ProAct65 trial will explore and evaluate the potential for increasing physical activity among older people recruited through general practice. The trial will be conducted in a relatively unselected population, and will address problems of selective recruitment, potentially low retention rates, variable quality of interventions and falls risk.

**Trial Registration:**

Trial Registration: ISRCTN43453770

## Background

The health benefits of physical activity have been extensively reviewed and evidence suggests that it reduces the risk of cardiovascular disease, type 2 diabetes, osteoporosis and certain cancers [1]. There is growing evidence of the association between regular physical activity and a reduced risk of all cause mortality [2], and of the potential savings for NHS budgets from exercise promotion for older adults [3]. Sedentary behaviour increases the risk of dependence, falls and fractures. Sustained levels of physical activity in adulthood maintain bone strength and can prevent fragility fractures in later life. Research has shown that a lifetime's history of regular physical activity can reduce the risk of hip fracture by up to 50% and much of this benefit is thought to result from a reduction in falls [4]. It is now clear that habitual physical activity and improved access to exercise opportunities is an important public health approach to the prevention of functional decline that can lead to frailty, falls and fractures [5].

Falls are common in people aged 65 years and older and can have serious consequences, including injury, pain, impaired function, loss of confidence in carrying out everyday activities, loss of independence and autonomy, and even death [6,7]. There is evidence that interventions providing some form of exercise may be effective in preventing falls amongst older people [8] and that healthcare costs [9,10] can be reduced if falls are reduced [11-15].

Current recommendations for health benefits are that people do at least 30 minutes of physical activity of moderate intensity on at least five days of the week [16]. However, surveys have consistently shown a high prevalence of physical inactivity in the UK population [17]. A recent systematic review comparing seventeen randomised controlled trials with different interventions designed to encourage sedentary, community dwelling adults to do more physical activity [18] concluded that interventions were effective in the short and mid term, at least in middle age, and that there were no significant increases in adverse events in the four studies that reported them. However, it is unclear which individual interventions (e.g. home-based or facility-based) are the most effective in increasing physical activity in the long term, or in specific groups (e.g. older people).

The NHS is attempting to address the problem of inactivity in a variety of ways, including exercise referral schemes in primary care ('exercise on prescription') which are currently provided by approximately 89% of Primary Care Trusts and usually involves referring patients to local leisure centres [19]. Although exercise on prescription has been shown to be feasible and effective in vulnerable older people [20], there appear to be significant barriers to the uptake of exercise classes in leisure centres. For many older people home exercise or group exercise in non-intimidating environments (e.g. community halls) may be more appealing, and result in higher uptake of exercise programmes and longer continuation of exercise. Peer activity mentors have also been shown to be effective in increasing uptake and adherence to exercise [21-24].

There are currently two existing exercise programmes, designed for use in community settings, specifically for people aged 65 and over. The first is a home based programme known as the Otago Exercise Programme (OEP) and the second is a community based group exercise programme known as the Falls Management Exercise Programme (FaME).

The OEP (Otago Exercise Programme) [25-31] and FaME (Falls Management Exercise) programmes [32] were both designed for use in community settings. specifically for people aged 65 and over. As well as being designed to reduce falls, both are based on the components of fitness and principles of programming for all older adults (i.e. warm up, mobility, stretches, strength and balance, endurance and a cool-down) and have all the elements of training appropriate for that age group. Exercises are tailored to the individual's ability and health need. Both programmes involve strength & balance training which is tailored to the individual's ability and health need.

This trial aims to fill the gaps in the current evidence base by evaluating the delivery, impact, acceptability and cost-effectiveness of a community based exercise programme (FaME) and a home based exercise programme (OEP) supported by similarly aged (peer) mentors, compared with usual care for primary care patients. The underlying assumption is that the exercises will produce sufficient subjective well-being and improved mobility to encourage continuation of higher levels of physical activity after the cessation of the intervention. Each exercise programme will be compared with usual care for effectiveness in producing sustained change in physical activity. The two programmes will be compared for cost-effectiveness if both are effective in promoting sustained change in physical activity. The primary hypotheses are: 1) Both exercise programmes produce sustained changes in physical activity (PA) compared with usual care, and 2) The Otago programme (OEP) is more cost effective than FaME

## Objectives

The primary objective is to determine the effect of two evidence based exercise programmes designed for older people, compared with usual care (i.e. with no special interventions to promote physical activity) on the achievement of recommended physical activity targets 12 months after cessation of intervention.

The secondary objectives are to:

(1) determine the health benefits of the programmes to participants starting at various levels of physical activity, particularly the effects on physical and psychological status, health status, health-related quality of life and quality adjusted life years (QALYs).

(2) estimate the costs of the exercise interventions, and possible cost offsets, and to assess the cost-effectiveness of community group exercise, and home-supported exercise compared with each other, and with usual care.

(3) determine the acceptability of the programmes, adherence rates, enabling factors and barriers to future implementation.

(4) compare the time course of responses by participants in terms of exercising at the recommended levels, at 0, 6, 12, 18 and 24 months after cessation of the intervention, between those undergoing the exercise programmes, and those receiving usual care.

(5) determine participants' perceptions of the value of exercise, and the predictors of continued exercise.

## Design/Methods

A 3 arm parallel design cluster controlled trial using minimisation for allocation at the level of general practice in two centres (London and Nottingham/Derby), comparing community-centre based group exercise programme (FaME), with a home based exercise programme and walking plan (OEP) and with usual care. There will be two years' follow-up to determine the impact, acceptability and adherence to the programme, longer term continuation of exercise and cost-effectiveness. The CONSORT diagram [35] summarises the design (Fig 1).

**Figure 1 F1:**
[figure not shown]
**Consort flowchart for cluster randomised trials; potential flow of participants**.

### Participants

Participants will be patients aged 65 years and over registered with participating general practices who give informed consent to participate.

#### Inclusion criteria for practices

Inclusion criteria will be a commitment to participate over the duration of the study and the availability of a suitable community venue in the practice catchment area.

#### Inclusion criteria for participants

Those aged 65 years and older, who can walk around independently of personal help both indoors and outdoors (with or without a walking aid) and who would be physically able to take part in a group exercise class, will be eligible to participate.

#### Exclusion criteria for participants

Those with any of the following criteria will be excluded:

• Three or more self-reported falls in the previous year;

• Resting BP > 180/100 mmHg; tachycardia > 100 bpm; those considered by their GP to have uncontrolled hypertension; significant drop in BP during exercise recorded in the medical records or found at initial assessment;

• Psychiatric conditions which would prevent participation in an exercise class, e.g. psychotic illness;

• Uncontrolled medical problems, which the GP considers would exclude patients from undertaking the exercise programme; e.g. acute systemic illness' such as pneumonia, poorly controlled angina, acute rheumatoid arthritis, unstable or acute heart failure;

• Conditions requiring a specialist exercise programme, e.g. uncontrolled epilepsy, significant neurological disease or impairment; unable to maintain seated upright position or unable to move about independently indoors;

• Not living independently (e.g. residential or nursing care);

• Significant cognitive impairment (unable to follow simple instructions);

• Already receiving long term physiotherapy or already in an exercise programme.

Exclusion criteria will be checked at the recruitment appointment by the researcher. This will include measurement of resting BP and pulse and completion of a health questionnaire. The participant's GP will be asked to confirm eligibility for each potentially eligible participant.

#### Recruitment of practices

General practices will be recruited from the Primary Care Research Networks (PCRN) in London and Nottingham/Derby. The PCRNs will be asked to identify potential participant practices by size and deprivation status. Approaches by mailed invitation, telephone contact with practice managers, and personal contact with local GP opinion leaders all be used as necessary [36].

#### Recruitment of participants

Practices will produce a single numbered list of patients aged 65 and over. Practice staff will be allowed to make and justify their own exclusions in liaison with the research team. The research team will provide the practices with a random number list to select the sample of patients to be approached after exclusions have been made. The sampling will vary depending on practice size. In practices with fewer than 600 patients aged 65 and over, all patients aged 65 and over will be invited to participate. In larger practices random sampling will be used to identify 600 patients aged 65 and over who will be invited to participate. Patients will then be sent invitation letters about the trial by their usual General Practitioner.

### Interventions

There are 3 arms to the trial:

(1) home based exercise programme and walking plan (OEP)

(2) community-centre based group exercise programme (FaME)

(3) usual care

#### Home based exercise programme (OEP)

This consists of a 30 minute programme of leg muscle strengthening and balance retraining exercises progressing in difficulty to be performed at home at least three times per week, and a walking plan to be undertaken at least two times per week for 24 weeks. Each participant will receive an instruction booklet and ankle cuff weights (starting at 0.5 kg) to provide resistance for the strengthening exercises. The programme will be introduced to participants by trained research staff, at an appropriate starting level determined at an initial assessment. Trained peer mentors will contact and visit the participants at home to start the exercise programme with them and will follow-up with up to three more home visits (as the participants require). Participants will record the days they complete the programme, and mentors will telephone them fortnightly as mentor support has been shown to be effective in increasing adherence [21-23]. Mentors will record and report any problems encountered with the exercise programme to the research team using an adverse event form developed for the study.

The delivery of the OEP will be standardised through training of research staff before the trial starts and there will be regular contact with the participants and peer mentors to check delivery protocols are being followed.

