#### Community based exercise programme (FaME)

The FaME programme comprises one hour-long PSI-delivered group exercise class in a local community centre for a maximum of 15 participants, and two 30 minute home exercise sessions (based on the OEP) per week for 24 weeks. Participants will be advised to walk at least twice per week for up to 30 minutes at a moderate pace. The programme includes leg muscle strengthening and balance retraining that progress in difficulty. Progressive trunk and arm muscle strengthening, bone loading, endurance (including walking) and flexibility training, functional floor skills (see below) and adapted Tai Chi complete the evidence based programme. Ankle cuff weights, Therabands (elastic resistance training bands) and mats are also used throughout the programme. The group exercises include retraining of the ability to get up from the floor and floor exercises to improve strength, balance and coping strategies to reduce the risk of complications resulting from a long lie [34].

The delivery of the FaME programme will be standardised through training of PSIs before the trial starts and there will be regular quality assurance visits for the FaME classes to check delivery protocols are being followed.

The PSI will keep a register of attendance and record tailoring of the programme and any feedback from participants. They will follow up non-attenders by telephone as necessary, recording any positive or negative feedback, and notify the research team about reasons for non-attendance or drop-out. Participants will be given a booklet containing their home exercise instructions.

FaME groups will contain 9 or 10 participants, so there will be 4 or 5 classes per week for each of the practices allocated to this arm. The number of PSIs running these classes will be determined by their availability, but the aim is to maximise continuity and standardisation in physical activity training, so the ideal would be to have one PSI who would lead all groups in one practice. This may be difficult to achieve, but we will report the actual deployment of PSIs in our findings. The same applies to peer mentors for OEP classes

General practitioners in participating practices allocated to either the FAME or OEP programmes will be discouraged from referring participants involved in the trial to other exercise therapy projects, outside the study.

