#### Ascertainment of outcomes

The following functional assessments will be used by researchers at baseline and at the end of the interventions (and at 6 months after allocation in the usual care arm):

1. Modified Clinical Romberg Static Balance test, eyes open and closed [39].

2. Timed get-up and go (with and without distraction) (TUG) as a measure of balance and falls risk [40].

3. Functional Reach as a measure of balance and falls risk [41].

4. 30 second chair rise as a measure of lower limb strength and power [42].

The following validated tools will be used at baseline, and as self-completion questionnaires at follow-up:

1. Confidence in balance measured by the ConfBal scale [43]. A total score is provided as a measure of confidence.

2. Confidence in carrying out a range of basic activities of daily living without falling measured by the Falls Efficacy Scale-International (FES-I) [44].

3. Readiness to change measured by the transtheoretical model [45] and applying it to exercise behaviour to determine perceived barriers [46] and self efficacy for exercise [47].

4. Quality of life will be measured using Older People's QoL Questionnaire (OPQOL) [48-50]

5. Social network size and density will be measured using the brief Lubben Social Network scale [51] and perceived social support measured by the Multidimensional Scale of Perceived Social Support (MSPSS) [52].

6. Subjective Habitual Physical Activity will be assessed using a number of validated questionnaires to ensure all domains of activity and sport are considered, including the Phone-FITT, PASE and CHAMPS [53-55] and the current level of activity questions used in the Household Survey [56].

7. Attitudes and beliefs about falls prevention interventions will be measured using the AFRIS questionnaire [57].

8. Falls risk will be measured by the Falls Risk Assessment Tool (FRAT) [58].

9. Health- related quality of life will be measured by the SF-12 [59]. Quality Adjusted Life Years (QALYs), which are the main outcome for the economic analysis, will be based on EQ-5D utility weights obtained by transforming SF-12 scores [38].

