### Blinding

It is difficult for participants to be blind in trials of exercise interventions, and for researchers to be blind to the allocation of participants as they will recruit participants and undertake baseline and follow up assessments. The researchers assessing outcomes are not blinded for pragmatic reasons only; the study is funded to support only enough researchers to carry our recruitment and follow-up simultaneously. However, general practices and their participants, and researchers having contact with practices and participants will not have foreknowledge of the treatment arm allocation of the practice, which will not be disclosed until after all participants within a practice have been recruited. Also, for the statistical analysis of participants' data, the statistician will be blind to the treatment arm allocation of the practices.

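### Research staff introduce the home programme and unblinded researchers measure function at its end, with no stated separation of roles, so the OEP arm may carry observer bias beyond that possible in every arm

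*Protocol article*

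**What the plan says.** **Delivery.** Under Home based exercise programme (OEP), "The programme will be introduced to participants by trained research staff, at an appropriate starting level determined at an initial assessment". The same section standardises OEP delivery by training research staff, and adds that "there will be regular contact with the participants and peer mentors to check delivery protocols are being followed", without naming who makes that contact. Continuing support comes from others: "Trained peer mentors will contact and visit the participants at home to start the exercise programme with them", followed by up to three further visits and fortnightly calls.

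Under Community based exercise programme (FaME), "The FaME programme comprises one hour-long PSI-delivered group exercise class in a local community centre". Here it is the PSIs who are trained to standardise delivery, and "there will be regular quality assurance visits for the FaME classes to check delivery protocols are being followed"; the visitors are not named. Usual care participants are offered neither programme.

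**Measurement.** Under Ascertainment of outcomes, "The following functional assessments will be used by researchers at baseline and at the end of the interventions", with the usual care arm tested "and at 6 months after allocation in the usual care arm". The tests are the Romberg balance test, timed get-up-and-go, functional reach and the 30-second chair rise.

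**Blinding.** The Blinding section states: "The researchers assessing outcomes are not blinded for pragmatic reasons only". It explains that funding covers only enough researchers to run recruitment and follow-up together, and that the researchers who recruit also do the baseline and follow-up assessments. It exempts no arm and does not mention that research staff introduce OEP.

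**The concern.** Lack of blinding is disclosed and applies to the whole trial. What is not discussed is that research staff have a part in delivering one of the three arms. An assessor who started participants on a programme may have both familiarity with them and an interest in their progress. The four tests depend to some degree on instruction, encouragement and the participant's effort, so an assessor can influence the result without intending to.

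If this happens more in OEP practices than elsewhere, it does not cancel between arms. It would shift OEP v usual care and OEP v FaME on the functional part of the first secondary objective. A reader could then take an assessor effect for a gain in balance or strength.

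**Working it through.** **1. Roles by arm, from the protocol text**

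| | OEP | FaME | Usual care |
|---|---|---|---|
| Introduces or teaches | Research staff introduce; peer mentors start it at home and support it | PSIs | No programme |
| Checks delivery | Regular contact, person not named | Quality assurance visits, person not named | None described |
| Does the end-of-programme functional tests | Researchers | Researchers | Researchers |
| Assessor blinded | No | No | No |

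The last two rows are the same in all arms, so ordinary unblinded-assessor bias is possible in each. The second row does not distinguish the exercise arms by who does the checking. Only the first row differs in the role of research staff: they have a stated delivery task in OEP alone.

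**2. Where in the data the bias could enter.** Concealment of allocation says that researchers doing baseline assessments do not know the arm until the practice has finished recruiting. Baseline tests are therefore protected and the end-of-programme tests are not. Adjusting for the baseline value, as Statistical methods plans, cannot remove an error that arises only at follow-up.

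**3. Which outcomes.** Follow-up data collection makes the assessments at 6, 12, 18 and 24 months after the intervention postal. The 12-month primary endpoint involves no researcher measurement. The mechanism is confined to the four tests.

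**4. Reproducing the plan's sample size** (Sample size section)
- 14.6% v 4.9%, 90% power, 5% two-sided, with continuity correction: 215 per arm, as stated (195 without the correction).
- Design effect 1 + (32 − 1) × 0.01 = 1.31; 215 × 1.31 = 281.65, so 282, as stated.
- 282 / (1 − 0.30) = 402.9, so 403, as stated.

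**5. Illustration of size.** The protocol gives no bias size and no ICC for the functional tests. Assume 282 with data per arm, design effect 1.31 (effective 215), a normal test at 5% two-sided, no true difference, and an extra bias b (in SD) in OEP beyond whatever bias the arms share.
- SE of a standardised difference = √(2/215) = 0.0964.
- Difference detectable with 90% power = (1.96 + 1.2816) × 0.0964 = 0.313 SD.
- False-positive rate = Φ(−1.96 + b/SE) + Φ(−1.96 − b/SE).

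| b (SD) | b/SE | False-positive rate | b as share of 0.313 |
|---|---|---|---|
| 0 | 0 | 5.0% | 0 |
| 0.05 | 0.518 | 8.1% | 16% |
| 0.10 | 1.037 | 17.9% | 32% |
| 0.20 | 2.074 | 54.5% | 64% |

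**6. Sensitivity to the ICC.** The Sample size section also cites 0.02 as an upper value for physical activity. The design effect is then 1 + 31 × 0.02 = 1.62, effective n = 282 / 1.62 = 174, SE = √(2/174) = 0.107, and the three rates become about 7.5%, 15% and 46%. The pattern does not depend on the choice of ICC.

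**The case against.** Much of the case on the other side stands.

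- **Bias in OEP only.** A reader might infer that observer bias enters OEP and spares FaME and usual care. The Blinding section does not support that: assessors are unblinded throughout, so both intervention-control comparisons are exposed. The OEP role can only add to this.
- **Coaching by researchers.** A reader might infer that researchers coach OEP participants throughout. The text says they introduce the programme; the continuing relationship is with the peer mentor.
- **Monitoring as an OEP-only researcher task.** The person who makes the OEP contacts is not named, and FaME has its own quality assurance visits and instructor reports to the research team. Monitoring therefore does not separate the two exercise arms.
- **The same individual in both roles.** The document speaks of research staff in one place and researchers in another, and never says that one person does both tasks for a participant. Overlap is an inference from limited staffing. A journal article may also leave assessor rotas and test scripts to the full protocol.
- **Objective measures and narrow scope.** Three of the four tests are a timing, a distance and a count, which limits discretion in scoring, though not in encouragement. The first secondary objective also covers psychological status, health status and quality of life, which these tests do not measure. For OEP v FaME, the Sample size section already expects little power for modest differences.
- **Assumed magnitude.** The bias values have no source in the document, and the effective sample size belongs to a different, binary outcome.

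What remains is that the Blinding section justifies unblinded assessment by the recruitment and follow-up workload alone. It does not deal with the added delivery role in one arm.

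**Conclusion.** The point holds as a possible additional, arm-specific bias in four secondary outcomes. All arms are open to observer bias; OEP may carry more of it because research staff introduce that programme and the stated procedures do not keep the introducing and testing roles apart.

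The amount cannot be derived from the protocol. Under the stated assumptions, 0.05 to 0.20 SD of extra bias would raise the false-positive rate from 5% to between about 8% and 54.5%, and 0.10 SD is about a third of the difference detectable with 90% power. These figures show sensitivity and are not estimates. They assume that the role overlap occurs, that the extra bias favours OEP, and that 215 effective participants per arm is a fair value for these tests.

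A reader might extend the concern to the main result. The documents do not support that: the 12-month primary endpoint is self-completed by post. It may be subject to reporting by unblinded participants, but that is a different problem. The sample size is unaffected. This is a worthwhile low-cost improvement and not a flaw that undermines the trial.

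**What to change.** Add to Ascertainment of outcomes and to Blinding:

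1. Where a centre has more than one researcher, anyone who recruited in a practice or introduced OEP there does not carry out its 24-week functional tests. Existing researchers exchange practices for those visits.
2. The exchange applies in all three arms, so that a change of assessor does not itself reveal the allocation.
3. Assessors follow a fixed script for instructions and encouragement, and are not told the practice's arm where that is feasible.
4. The assessor is recorded at each visit.
5. Where exchange is not possible, the assessor is still recorded and the overlap is reported as a limitation of the functional comparisons.

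The Blinding section should also state that research staff introduce OEP.

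**Cost.** No added visits, and no added staff where a centre already has more than one researcher; the protocol does not give numbers per centre, hence item 5. There is some travel and rota work, and less continuity between a participant and one researcher. The exchange removes familiarity with the participants tested, but not any general stake a researcher has in OEP from introducing it elsewhere.
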